### Data collection methods

Data on goal-attainment in parenting skills (COPM) will be collected by the PYC-practitioners. A manual has been designed to reduce the risk of measurement error and each PYC-practitioner will partake in an instructional workshop on the COPM before starting data collection. The remaining data will be collected by the researchers or PYC-practitioners in interviews with the participants. The study-specific forms have been piloted for comprehensibility, and a manual has been developed to ensure standardised implementation.

### Retention

The PYC-practitioners will use a recruitment logbook to document participants who discontinue the intervention. To improve retention, the parents will receive a 100 SEK gift card at each data point (pre, post, follow-up, and interview), and the children will receive a book after the interview.

### Data management and confidentiality

Data will be managed and stored according to the General Data Protection Regulation in the EU and the data management policy at Örebro University. All participant information, interviews, and questionnaires will be stored in a password-protected storage system at Örebro University. Participants’ identity information will be replaced with code numbers, and the researchers will inform the PYC-practitioners about each participant’s code. A code list that links the participants’ identities to their unique codes will be established and stored separately from the research data in an encrypted file on a password-protected server. Only authorised staff will have access to these files. Data on paper forms collected by social workers will be stored securely at the social services facilities until they are transported to Örebro University. All researchers will have access to the data throughout the project.

### Patient and public involvement

A range of representatives for patients and the public has been and are involved in the design and conduct of this study. This includes representatives from patient organizations for people with ID, ADHD and ASD, the SUF Resource Center for parents with disabilities as well as the social service providers who assisted in collecting. These representatives were involved from the initial planning stage before funding was obtained. Since funding was secured, a reference group of representatives have continuously been consulted regarding design, practical implementation, burden of intervention and measures, and recruitment strategies. Further, they will be involved in the dissemination and implementation of study results.

### Statistical methods

Baseline characteristics will be reported by using summary statistics such as frequencies and proportions and mean/SD or median/IQR depending on the data distribution. The normality of outcome data will be assessed using the Shapiro–Wilks test. The primary comparison will be the change in goal-attainment (COPM) as rated by the parent and the PYC-practicioner, respectively, from baseline to post-intervention. Sensitivity analyses will be employed to evaluate the robustness of the results. Secondary analyses will involve changes in parenting self-efficacy (PSOC) and children’s mental health (SDQ) as well as follow-up measures for all outcomes. Effect sizes will be calculated as Cohens *d*. The process evaluation will involve repeated measures analyses of COPM data. Two-sided tests with a significance level of *p* <  0.05 will be employed. Missing data will be handled according to the recommendations of Jakobsen et al [93].

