### Quantitative evaluation

The primary outcome variable is goal-attainment in increasing parenting skills according to PYC’s intervention domains. This is motivated by PYC’s purpose of increasing perceived and real parenting ability, and by the structure of PYC, because parents continuously set goals for the intervention. All quantitative outcomes will be examined pre- and post-intervention, and 6 months post-intervention.

Goal-attainment in parenting skills: Goal-attainment in PYC’s intervention domains will be measured with the Canadian Occupational Performance Measure (COPM) [65,66]. COPM is an individualised, client-centred outcome measure that captures clients’ self-perception of everyday issues that influence their performance in daily life. COPM provides a basis for setting concrete individual intervention goals and for detecting changes in perceived performance and satisfaction with performance over time. The parents will select goals for the PYC-intervention and rate their performance and satisfaction using a 10-point rating scale. The performance scale ranges from 1 (“not able to perform it at all”) to 10 (“able to perform it extremely well”), and the satisfaction scale ranges from 1 (“not satisfied at all”) to 10 (“extremely satisfied”). The scale has been adapted with facial expressions illustrating each response option in order to facilitate responses. COPM assessments on parents’ performance will be gathered from both parents and PYC practitioners pre- and post-intervention. 6-month follow-up data will only be gathered from the parents, since cases may often be closed, in which case practitioners are not allowed to be in contact with the parents and won’t be able to report on their performance.

The COPM has demonstrated good validity, reliability, and sensitivity to change [67], with an increase of two or more points indicating a clinically significant change [68]. The clinical utility of COPM has also been demonstrated [67,69], and it has been used with individuals of different ages and diagnoses, including mental illness, ID, and ADHD [70–72].

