### Sample sizes

For the quantitative evaluation, a preliminary sample size calculation for one group and two-sided t-test with 80% power, to allow testing at *p* =  0.05 and an effect size of *d* =  0.5 rendered a sample size of 34 participants. When calculating on group standard deviation on COPM-performance of 2.04 and an expected mean increase of 1.47 from Clarke et al [92] the target sample size was adjusted to n =  18 participants. To account for potential attrition of up to 25%, the study will therefore include n =  24 participants. For the qualitative evaluations, 15 parents who have received PYC will be included and all children aged 4 years or older whose parent have received PYC will be asked to participate, with the aim to recruit 8-10 children.

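### The single primary comparison is two tests (parent and practitioner ratings) at 0.05 each with no success rule, while the sample size covers one test

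*Protocol article*

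**What the plan says.** The section Quantitative evaluation defines the outcome without a rater or a scale: "The primary outcome variable is goal-attainment in increasing parenting skills according to PYC’s intervention domains". On the scales it says: "The parents will select goals for the PYC-intervention and rate their performance and satisfaction using a 10-point rating scale". On the raters it says: "COPM assessments on parents’ performance will be gathered from both parents and PYC practitioners pre- and post-intervention". So the parent gives two scores and the practitioner gives one, for performance only.

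Statistical methods then fixes the primary analysis: "The primary comparison will be the change in goal-attainment (COPM) as rated by the parent and the PYC-practicioner, respectively", from baseline to post-intervention. The error level is the same for every test: "Two-sided tests with a significance level of" p < "0.05 will be employed". The section gives no either/both rule, no testing order and no division of the 0.05.

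Sample sizes plans for "one group and two-sided t-test with 80% power". The final target rests on one variable: "When calculating on group standard deviation on COPM-performance of 2.04 and an expected mean increase of 1.47". This leads to 18 participants, raised to 24 for attrition of up to 25%. The scale is named there, but the rater is not.

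**The concern.** The text names one comparison but specifies two tests, and the sample size covers only one. A reader of the results cannot tell from the plan what counts as a positive primary result. If one significant rater is enough, the chance of a false primary finding exceeds 0.05. If both are needed, the planned 80% power does not apply to the claim. If the raters disagree, no primary answer is defined, and the choice could be made after seeing the data.

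Disagreement is foreseeable from the article itself. The Discussion describes the practitioner's rating as adding a different, arguably less subjective view, but warns that practitioners may in effect be rating their own effort. The Process evaluation section anticipates response shift in parents' ratings. In an uncontrolled pre-post study, a primary result fixed in advance is one of the few protections available.

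The open choice of parent scale adds a possible third candidate, parent-rated satisfaction.

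**Working it through.** **Inputs.** From Sample sizes: mean increase 1.47, SD 2.04, power 80%, one-group two-sided t-test, attrition up to 25%. From Statistical methods: two raters, two-sided 0.05 for each test. From Quantitative evaluation: the parent rates two scales and the practitioner one, so there are at most three candidate primary tests. The article does not give the correlation r between the parent's and practitioner's change scores; I assume 0 to 0.9. Nor does it give an effect for each rater; I assume the same effect for both where needed.

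**1. The plan's own figure.** The standardised effect is d = 1.47 / 2.04 = 0.7206. For a one-sample t-test with n − 1 degrees of freedom and noncentrality d√n, power at two-sided 0.05 is 0.797 at n = 17 and 0.821 at n = 18. So n = 18, and 18 / 0.75 = 24. The preliminary calculation with d = 0.5 gives power 0.795 at 33 and 0.808 at 34. Both stated figures reproduce for a single test.

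**2. Either rater suffices.** With independent tests the family-wise error is 1 − (1 − 0.05)² = 0.0975. For three tests it is 1 − 0.95³ = 0.143. With correlation, from simulated paired t-tests at n = 18 (200,000 runs per setting):

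| r | two tests | three tests |
|---|---|---|
| 0 | 0.098 | 0.143 |
| 0.5 | 0.092 | 0.127 |
| 0.7 | 0.085 | 0.112 |
| 0.9 | 0.070 | 0.086 |

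These are two-sided figures. About half of each lies in the direction of improvement.

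**3. Both raters must succeed, 0.05 each.** The error is at most 0.05. With d = 0.72 for both raters and r = 0, joint power is the square of the single-test power: 0.821² = 0.675 at n = 18. Simulation gives joint power at higher correlation:

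| analysed | r = 0 | r = 0.5 | r = 0.9 |
|---|---|---|---|
| 18 | 0.68 | 0.71 | 0.77 |
| 22 | 0.80 | 0.82 | 0.86 |
| 24 | 0.85 | 0.87 | 0.90 |

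At r = 0, n = 21 gives 0.881² = 0.776 and n = 22 gives 0.8965² = 0.804. So 22 is the smallest number that secures 80% across the range. Higher correlation needs fewer: about 21 at r = 0.5 and about 19 at r = 0.9.

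**4. Splitting the 0.05 over two raters.** At 0.025 each, power per test at n = 18 falls to 0.72. Reaching 80% needs 21 analysed, and 21 / 0.75 = 28 enrolled.

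**The case against.** The strongest reply is that the article condenses a fuller plan, and multiplicity rules often sit in an analysis plan that is not shown. That would answer a complaint about missing detail. It does not answer this one: the article itself gives two raters primary status, gives every test 0.05 and sizes the study for one test.

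A second reply is that the two ratings may be meant as two separately reported conclusions, one on perceived change and one on change as the practitioner sees it. Each conclusion would then keep its own 5% error. This is a fair reading, but the article does not state it, and it sits badly with a single primary outcome and a single primary comparison.

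Three stronger inferences are tempting, and the document does not support them:

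- A reader might infer that the primary claim carries twice its stated error rate. That needs one significant rater to be enough and nearly independent ratings. The article states neither. Both raters score the same parent's performance, so positive correlation is likely, and a both-must-succeed rule gives no inflation.
- A reader might take the three-test figure as the main result. Sizing on performance, and having practitioners rate only performance, both point to performance as the intended scale. The 0.14 is an outer bound.
- A reader might assume that the sample size was built on the parent's rating. The section names the scale but no rater.

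The power shortfall is also conditional: it applies at 18 analysed, the full 25% loss, and 25% is stated as an upper limit.

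**Conclusion.** The point holds as a defect in how the primary comparison is fixed; the sample-size arithmetic is correct. If either rater suffices, the family-wise error is about 0.07 to 0.10 for correlation 0.9 to 0, and up to 0.14 if parent satisfaction is also counted and the tests are independent. If both must succeed, error is controlled and joint power at the planned 18 analysed is about 0.68 to 0.77. The power figures assume d = 0.72 for both raters, which the article does not state for either rater separately. The size of the problem depends on a rule that the plan does not give, so no single inflated error rate can be attributed to it. It should be corrected before the data are analysed, but it does not invalidate the design.

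**What to change.** Amend the plan with a dated change, made without reference to accrued results. Fix COPM performance as the primary scale, and name one rater's change from baseline to post-intervention as the sole primary test at two-sided 0.05. The parent is a reasonable choice, being the only rater followed to 6 months. This is a recommendation, because the sample-size section does not settle the rater. Make the other rater's performance score, then parent satisfaction, either secondary or tested in that fixed order after the primary.

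Under this option the 18 analysed and 24 enrolled stand. The cost is that one rater loses co-primary status. The change is short, but it needs care: recruitment began in September 2022 and an interim analysis is planned at half the data, so the amendment should record what had been seen when the choice was made.

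Alternatively, keep both raters, state that both must be significant at 0.05, and restate the power as joint power (about 0.68 to 0.77 at 18 analysed, under the assumptions above). If instead either rater is to count, splitting the 0.05 equally needs 21 analysed and 28 enrolled.

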### Qualitative analyses

Content analysis and reflexive thematic analysis will be used for the parent and child interviews as appropriate [94,95,96]. The material will be coded by one researcher, and the codes will be reviewed by two co-authors. All co-authors of the resulting manuscript will participate in interpretation and discussion.

### Data monitoring

A formal data monitoring committee is not needed due to the minimal risks associated with participation. As such, stopping guidelines are not deemed necessary. An advisory group has been established, consisting of professional and NGO-organisations representing persons with IDDs. The research group will report to the advisory group and discuss any need for modifications or early termination of the data collection. An interim analysis will be performed when 50% of the data have been collected, and data collection will be stopped when the required number of participants is reached or when the principal investigator makes such a decision.

An adverse event is defined as any untoward occurrence believed to be causally related to participation in the study and that might result in inadequate caregiving or poor child safety. All adverse events occurring after study entry will be documented. The study will also examine the potentially negative effects of PYC through interviews with parents and children.

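### The planned 50% interim analysis, with stopping left to the principal investigator and no criterion, permits stopping on a favourable result while the final test stays at an unadjusted 0.05

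*Protocol article*

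**What the plan says.** The Data monitoring section of the protocol article makes three statements that belong together:

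- "An interim analysis will be performed when 50% of the data have been collected".
- On the ground of minimal risk, there is no data monitoring committee and "stopping guidelines are not deemed necessary".
- "data collection will be stopped when the required number of participants is reached or when the principal investigator makes such a decision".

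The section also foresees discussing early termination with an advisory group, and gives no criteria. It does not state the purpose or content of the interim analysis.

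Statistical methods prescribes "Two-sided tests with a significance level of" 0.05 and mentions no adjustment for an earlier look. The primary comparison is the change in COPM from baseline to post-intervention. Sample sizes plans a single analysis: "one group and two-sided t-test with 80% power", with a "group standard deviation on COPM-performance of 2.04 and an expected mean increase of 1.47", giving 18 participants, raised to 24 for attrition. Data management and confidentiality gives all researchers access to the data throughout the project.

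**The concern.** The reason given for having no stopping guidelines concerns participant safety. It does not deal with the statistical consequence of looking at results and then choosing whether to continue. In a single-arm pretest-posttest study, any summary of COPM change at the interim is the effect estimate itself. No independent body stands between that result and the decision to stop.

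Two things are at stake. First, a study that may stop on a significant half-way result, and otherwise tests again at 0.05, does not hold a 5% error rate. Second, when the true effect is positive, studies that stop early are those whose first half happened to look good, so their estimate is too large. The article says that only one quantitative study of PYC exists and none from Sweden, and it plans to report Cohen's d. An inflated estimate would therefore carry weight.

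**Working it through.** **Inputs from the article.** Two-sided alpha 0.05 (Statistical methods). Mean increase 1.47, SD 2.04, target 18, enrolment 24 (Sample sizes). One interim at 50% (Data monitoring), so looks at 9 and 18 if the count is of evaluable participants, or at 12 and 24 if it is of those enrolled.

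**Assumption not in the article.** The interim tests COPM change at 0.05, and a significant result ends the study with no further data.

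**1. The plan's own figures.** Power of a one-sample two-sided t-test comes from the noncentral t with n − 1 degrees of freedom and noncentrality d√n.

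- d = 0.5: n = 33 gives 0.795 and n = 34 gives 0.808, so 34 is reproduced.
- d = 1.47/2.04 = 0.7206: n = 17 gives 0.796 and n = 18 gives 0.821, so 18 is reproduced, with 2.04 used as the SD of the change.
- Attrition: 18/(1 − 0.25) = 24.

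These are correct for a design with one analysis.

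**2. Type I error with two looks at 0.05.** In normal theory the two statistics have correlation √0.5 = 0.707, and P(|Z₁| > 1.96 or |Z₂| > 1.96) = 0.083. Simulated t-tests give:

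| Looks | Type I error |
|---|---|
| 9 and 18 | 0.085 |
| 12 and 24 | 0.084 |

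**3. Size of the estimate when the true change is 1.47.** The chance of stopping is the power at the first look. The means are simulated.

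| Looks | Chance of early stop | Mean estimate if stopped | Mean over all studies |
|---|---|---|---|
| 9 and 18 | 0.48 | 1.96 (1.96/1.47 = 1.34) | 1.59 (1.59/1.47 = 1.08) |
| 12 and 24 | 0.62 | 1.79 (1.79/1.47 = 1.22) | 1.57 (1.57/1.47 = 1.07) |

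**4. Other readings of the interim.** If it is purely administrative, alpha stays at 0.05. If it can stop only on an unfavourable trend (interim mean change at or below zero), alpha for looks at 9 and 18 falls to about 0.025.

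**5. Limits that would hold 5%.** A two-look O'Brien-Fleming rule solves P(|Z₁| > c√2 or |Z₂| > c) = 0.05, which gives c = 1.977. That is p < 0.0052 at half and p < 0.048 at the end. Simulated t-tests give an overall error of 0.051 for both sets of looks. Power at the planning effect with n = 18 goes from 0.821 to about 0.818.

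**The case against.** The strongest reply is that the article never says the interim tests COPM, uses 0.05, or leads to stopping on a good result. The statement on guidelines follows from the minimal-risk argument and reads as a safety remark. An advisory group is to be consulted on early termination, and interim content and boundaries are often left to an analysis plan, which is not shown. This stands as far as it goes: the error rate is permitted to rise, and it cannot be said that it will. It does not remove the point. The article is not silent: it commits to the interim, rejects stopping guidelines and grants a discretion without limits. An analysis plan could restrict this only by overriding the stated rule. The advisory group is not described as deciding without sight of outcomes.

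The size also depends on a hard stop. The intervention typically lasts 6–12 months, so some parents would probably be mid-treatment at the interim. If, as an assumption, 4 to 8 of them still contributed after a stop at 9, the estimate would fall to (9 × 1.96 + 4 × 1.47)/13 = 1.81, or (9 × 1.96 + 8 × 1.47)/17 = 1.73. The +34% is therefore the upper end.

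Finally, a pretest-posttest design without controls cannot establish that PYC caused a change, and the authors concede that it is weaker. That makes the excess error a secondary threat to causal claims. It leaves the stated 5% and the reported effect size unprotected.

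**Conclusion.** The point holds in conditional form. The article's own wording allows data-dependent stopping with an unadjusted final test. If the interim tests COPM change at 0.05 and significance stops the study, type I error is about 8.4–8.5%. With a true change of 1.47 points and SD 2.04, the estimate is too high by 7–8% on average and by 22–34% among studies stopped early. The ranges cover looks at 12/24 and 9/18 and assume normally distributed changes.

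Three stronger readings are not supported:

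- A reader might infer that the plan does raise the error rate and does bias the effect upward. The purpose of the look is not stated, and an administrative look leaves alpha at 5%. Under no effect with two-sided stopping, the mean bias is zero.
- A reader might add the parent and practitioner ratings to reach a larger combined error. That is a separate multiplicity question, and it needs a rule that either rater's result suffices, which the article does not state.
- A reader might call the required number ambiguous between 18 and 24. Sample sizes says that 24 will be included, and the conclusion is the same for both.

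**What to change.** - State that the 50% look covers recruitment, data completeness and the COPM standard deviation only, with no pre-post test or estimate.
- Replace the discretion clause with wording such as: data collection ends when the 24 planned parents have been enrolled and followed; earlier termination is only for safety or feasibility, decided without sight of outcome results.
- If an efficacy look is wanted, specify a two-look O'Brien-Fleming boundary: p < 0.0052 at half and p < 0.048 at the end.
- If the interim has already taken place, report what was examined, by whom, and who decided to continue or stop. Recruitment began in September 2022 with a planned end in June 2025, and the article does not say whether the look has occurred. New wording cannot undo a look already taken.

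If the interim is still to come, the cost is a change of text. No further participants are needed, and the O'Brien-Fleming option costs about 0.3 percentage points of power at n = 18 (0.821 to 0.818).

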### Qualitative evaluation

Qualitative methods will be used to explore the participants’ perspectives and perceptions.

Parents’ experiences: Parents’ experiences of PYC will be explored with semi-structured interviews. Parents will be interviewed individually, at a location of their choice, shortly after they complete PYC. A study-specific interview guide adapted for individuals with IDDs will be used [3]. The interview questions will include perceptions of parenting skills before and after PYC, positive and negative aspects of PYC, and PYC’s influence on parent-child relationships and other parts of their lives (e g, relationships).

Children’s perspectives: The children’s perspectives will be gathered through age-appropriate, semi-structured interviews, after their parents have received PYC. Children will be interviewed individually; at a place they and their parents have chosen. A study-specific interview guide has been designed, with age-appropriate wordings and time frames [84]. Children will be asked about their everyday activities and experiences, with different family members, in relation to different emotions. Both positive and negative emotions will be explored. Pictorial support will be used to facilitate children’s recollection and communication, influenced by methods using pictures and photos in interviews with children with and without disabilities [85–90]. To keep the children’s interest and attention, questions about what an ordinary day looks like are interspersed with tasks where the child can use pictures to tell the story [84]. First, pictorial support in the form of a circle will depict ordinary weekday and weekend days, respectively, with pictorial anchor points for waking up and morning routines(pre)school, extracurricular activities and family time, evening routines and going to bed. Additional pictorial support will be used, divided into pictures of morning and evening routines, important people, indoor and outdoor activities, and expressions of positive and negative emotions. The use of both visual and verbal parts helps children express their thoughts and possibly raise sensitive aspects of their family life [91].

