### Ancillary and post-study care

The parents’ ability to provide safety and meet their children’s needs may decline during the study. In such cases, necessary measures will be taken immediately in accordance with the Social Services Act. Parents will be interviewed by experienced researchers and social workers or similar. The interviewed children will be given the opportunity to talk about their experiences and feelings connected to their parent’s participation in PYC. The children will be met by a researcher with extensive experience in interviewing children who will treat them respectfully, and such conversations can serve as a tool to help the child process unpleasant experiences or events.

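### An event is documented as adverse only if participation is believed to have caused it, so the count cannot show how many events bearing on caregiving or child safety occurred

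*Protocol article*

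**What the plan says.** The Data monitoring section sets two conditions for an adverse event. The first is causal: "An adverse event is defined as any untoward occurrence believed to be causally related to participation in the study". The second concerns consequence: "and that might result in inadequate caregiving or poor child safety". The section then adds: "All adverse events occurring after study entry will be documented". The article describes no step in which an event is recorded first and its cause judged later, and it does not say who holds the belief.

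The same section gives a second route: "The study will also examine the potentially negative effects of PYC through interviews with parents and children". The Qualitative evaluation section times the parent interviews "shortly after they complete PYC" and the child interviews "after their parents have received PYC". The Sample sizes section says that "15 parents who have received PYC will be included" and aims for 8 to 10 children aged 4 or older.

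The Ancillary and post-study care section acknowledges that parents' ability to keep their children safe and meet their needs "may decline during the study". It refers such cases to measures under the Social Services Act and does not mention adverse event recording. The Retention section has practitioners log participants who discontinue; it states no enquiry about harms in that group.

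**The concern.** Harms are normally collected in two steps: write down what happened, then judge whether the intervention had a part in it. Here the second step decides whether the first takes place. An event that nobody attributes to participation leaves no adverse event record, so nobody can revisit the attribution.

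This matters more here than in many studies. The events at issue are foreseeable: the Introduction describes raised rates of child-protection involvement and out-of-home placement among these families. An observer can therefore easily put such an event down to the family's prior situation. With no comparison group, there is no background rate within the study against which to test that view.

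What is at stake is the statement on harms in the final report, together with the advisory group's discussion of modification or early termination, which depends on what has been recorded. The primary COPM comparison is not affected.

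**Working it through.** The plan gives no figure for harms, so the check sets the rules side by side.

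**Step 1: what the definition admits.** Crossing the two conditions gives four kinds of untoward occurrence.

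| | Believed caused by participation | Not believed caused by participation |
|---|---|---|
| Could compromise caregiving or child safety | documented as adverse event | not an adverse event |
| Could not | not an adverse event | not an adverse event |

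The concern is the upper right cell. A placement or a child-protection report attributed to other circumstances falls there.

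**Step 2: what the count can tell the reader.** Let N be the number of untoward occurrences that meet the consequence condition, and q the share of them believed related. The adverse event count is

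R = q × N.

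Only R is collected. Neither N nor q can be recovered from it, because the events that make up (1 − q) × N are not kept as adverse events. R = 0 is what one sees if N = 0, and also if N is positive and q = 0. If all N events were recorded with a separate relatedness item, N, R and q = R/N would all be available.

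**Step 3: whether the causal belief can be checked.** The Study design section describes a single-group pretest-posttest study. Relatedness can still be judged case by case on timing and circumstances, but not against an event rate in comparable families without PYC. No later review of the belief is described. The Discussion warns that a practitioner's rating of the parent may be perceived as an assessment of the practitioner's own effort. If practitioners also judge causality, which the article does not say, the same difficulty would arise.

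**Step 4: whether the interviews close the gap.** Parent interviews follow completion of PYC, and child interviews follow the parent's receipt of it. A family that stops early does not reach the first time point and may not be counted under the second. The interviews also come shortly after PYC, so they do not cover the period up to the 6-month follow-up. They can reveal perceived negative effects among those interviewed, but they cannot supply a count of events among all enrolled families.

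**Step 5: whether later events can be captured.** The Quantitative evaluation section says that cases may often be closed by 6 months and that practitioners may then have no contact. Practitioners therefore cannot be relied on as the source for that period. Parents are still assessed at 6 months, so they can be asked.

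**Size.** The document gives no event rate and no value for q. The share of events lost cannot be calculated.

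**The case against.** The strongest case on the other side is that deterioration would not be invisible. COPM, PSOC and SDQ are measured before, after and at 6 months and tested two-sided. Parents rate COPM monthly, practitioners rate the parent's performance before and after, and discontinuations are logged. Events believed related are documented for every participant from study entry, including those who later stop. An article also condenses a fuller protocol, which may set out reporting procedures. All of this stands, and it limits the point. It does not repair the definition: the scales show worsening among those measured but do not register a placement or a child-protection report, and the causal condition is a stated rule, not a detail left out.

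Several stronger readings are tempting, and the document does not support them.

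- *A reader might infer that all declines in parenting will go unrecorded.* The scales and logs above contradict this. The Ancillary and post-study care section says that a decline is possible, not that it is expected or that it is kept out of the records.
- *A reader might infer that only completing parents are asked about negative effects.* Children are interviewed too, the Sample sizes section speaks of parents who have received PYC, and no sentence excludes discontinuers. Their absence is probable, not stated.
- *A reader might put the unheard group at 25% × 24 = 6 families.* The 25% is an allowance for attrition in the sample size. A parent may finish PYC and miss an assessment, and nothing in the document shows that those who leave fare worse.
- *A reader might cite the one-sided 95% upper limit for 0 events in 24, 1 − 0.05^(1/24) = 0.117, or about 12%.* That limit follows from the sample size and applies under any definition, so it does not measure this defect.
- *A reader might conclude that a single-group study gives no basis at all for judging relatedness.* Case-by-case judgement remains possible, and the fix relies on it. The fault is that the judgement comes before recording and is not reviewed.

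The absence of a data monitoring committee is not part of this point; the section gives a reason for it and names an advisory group.

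**Conclusion.** The point holds in a limited form. The adverse event definition filters on believed cause before anything is documented, so the adverse event count will describe beliefs about relatedness and not how often events bearing on caregiving or child safety occurred. The interviews probably do not reach families who discontinue, and this limb is less certain than the first because it rests on the stated timing.

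The direction, towards under-recording, follows from the definition if at least one qualifying event is not believed related. The size cannot be computed from the document. The conclusion also assumes that no fuller protocol contains a separate record of unrelated events; the article describes none. This should be corrected, because a statement that no adverse events occurred could not be interpreted as it stands. The efficacy analysis is unaffected.

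**What to change.** 1. Delete the causal condition from the definition and keep the consequence condition. Document every untoward occurrence that meets it from study entry, whether or not it is believed related, and name out-of-home placement and new child-protection reports as examples.
2. Have the research team judge relatedness afterwards and record it as a separate item.
3. Have practitioners record events while they are in contact with the family, and ask parents a short question at the post-intervention and 6-month data collections already planned. This avoids relying on practitioners after a case is closed.
4. Report all events and related events separately. Recruitment began in September 2022, so state the date of the change and which events were collected under each definition.
5. Optionally, put the harms questions to discontinuing parents who agree to answer them.

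The cost is a longer list of events, many of which may be judged unrelated, a short added question at existing contacts, and the team's time to judge relatedness. The sample size and the planned number of interviews need not change. The article does not show whether the added question would need a notification to the ethics authority, so the sponsor should check. Nothing here alters how a decline in a child's care is handled.
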